## Methods of minimising bias

### Randomisation

Patients will be randomised to one of two groups using a pragmatic approach. A simple randomisation will be performed by the trial statistician using generation of a random number. The investigators will have no way of predicting, or of influencing the group to which the individual is randomised.

The two groups are as followed:

A – Receive an ^18^F-PSMA-1007 scan initially, followed by ^68^Ga-PSMA-11

B – Receive a ^68^Ga-PSMA-11 scan initially, followed by ^18^F-PSMA-1007

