| **Study Design** | *A prospective, single centre, open label, dual arm randomised cross-over, non-inferiority trial comparing the new tracer (^18^F-PSMA-1007) with the standard tracer (^68^Ga-PSMA-11) in biochemically recurrent prostate cancer.*  *The study is designed using the Standards of Diagnostic Accuracy (STARD) checklist. The study is initiated, planned and will be conducted and analysed by the investigators. Financial support is provided the Werner und Hedy Berger-Janser Foundation, the Bernese Cancer league and the Direktion Lehre und Forschung, Inselspital Bern. The second tracer for the second PET is provided by either SWAN Isotopen AG or Unilabor Bern. All data will be collected in a central trial database.* |
| **Inclusion / Exclusion criteria:** | *Inclusion Criteria*   - Patients with known biochemical recurrence of a histologically confirmed prostate cancer post radical prostatectomy, defined as two consecutive PSA values > 0.2 ng/ml: - Post prostatectomy: Patients > 18 y/o - PSA measured within ± 4 weeks of the first PSMA-PET/CT - Patients providing written informed consent - No change in PC treatment in the period between the first and second scans   *Exclusion Criteria*   - Patients receiving ADT within 6 months prior to the PSMA-PET/CT - Patients with contraindication to diuresis with 20mg Furosemide - Patients with renal dialysis or relevant renal impairment (eGFR < 35 ml/min) - Inability to provide written informed consent - Inability to schedule and attend two consecutive PET examinations - Patients undergoing active treatment for a second non-prostatic malignancy at the time of the first scan. - Known sensitivity or allergy to PSMA-ligands or one of the components of the radiotracer solutions used. |
| **Measurements and procedures:** | All patients will undergo scanning with both radiotracers, affording an intra-patient comparison of both tracer types. The PET scans will be analysed with respect to number of lesions detected and tracer uptake (SUV) for pathological lesions. |
| **Study Product / Intervention:** | In this cross-over trial, patients will be randomised to one of two tracer sequences, ^68^Ga-PSMA-11 first or ^18^F-PSMA-1007 first. Patients will undergo a scan with the first radiopharmaceutical, and a second scan at earliest after a period of 2 days and at latest 2 weeks. |
| **Control Intervention (if applicable):** | Intra-patient comparison with both radiotracers. |

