### Handling of Drop outs

Should a patient withdraw prior to completion of the second examination, that patient will be replaced and recruitment will continue until 100 patients have been recruited.

For patients who withdraw consent at any point, the data up to the time point of withdrawal will be used.

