## Determination of Sample Size

Power was determined using Monte Carlo simulations with 1000 repetitions and the following assumptions:

- Marginal probabilities: 80% of the patients are positive for tracer A and 80% are positive for tracer B
- Both tracers are applied to each patient
- Non-inferiority design with a one-sided alpha of 2.5%
- Non-inferiority margin of -10% (clinically acceptable margin in detection rate, balanced against the requirements for clinically realistic number of patients). We justify this margin as being less than 50% of the margin reported for superiority (22%) in a prospective trial published for ^68^Ga-PSMA-11 versus the first-generation tracer ^18^F-Choline [22].
- Non-inferiority is concluded if the lower limit of a 95% confidence interval (Wald with Bonett–Price Laplace adjustment) for the difference in the proportion of tracer-positive patients (new tracer – old tracer) is larger than the non-inferiority margin
- A pragmatic assumption is made regarding the correlation of the paired measurements. Limited data are available for this, given the dearth of comparative studies. Neither retrospective analyses [28] nor limited pilot studies [17, 27] have demonstrated any difference in detection rate. We take a worst-case scenario, and assume that both tracers are positive for 75% of the patients.

Data was simulated using function rmvbin from R package bindata [29]. With 100 patients we will have a power of 85% to detect non-inferiority.

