### Primary Analysis

The primary outcome (proportion of patients with PSMA-positive pathological lesions) will be compared between tracers using an absolute risk difference (new tracer minus old tracer) with a one-sided lower 95% confidence interval (CI) for paired proportions (Wald with Bonett–Price Laplace adjustment). If the lower limit lies above -10%, we will claim non-inferiority. Proportion of pathologic scans will be based on majority consensus reads.

The number of PSMA-positive lesions defined as pathological, benign and uncertain in each region will be analysed using separate mixed-effects Poisson regression models with tracer as fixed covariate and nested random effects for patient and region. We will report incidence rate ratios with 95% CI and p-values. As a sensitivity analysis we will compare the number over all regions using the Wilcoxon signed-rank tests and the Mann-Whitney statistic with 95% CI.

Inter-reader reliability will be analysed on the region-level based on the number of benign, pathological and uncertain lesions determined by each reader. We will calculate Krippendorff’s alpha with a ratio difference function and bootstrap 95% CI separately for each tracer.

Lesion-based PPV will be calculated for each tracer as the proportion of pathological lesions confirmed pathological during follow-up among all lesions with a known state and will be presented with 95% Wilson score CI. Using all lesions with a confirmed status during follow-up, the two tracers will be compared using McNemar’s test and an absolute risk difference with 95% confidence interval.

The semi-quantitative tumour to background ratio will be summarized on a region-level (i.e. using the mean over all positive lesions per region) and analysed using a linear mixed-effects regression model with tracer as fixed covariate and patient and region as nested random effects. The mean difference with 95% CI will be reported.

For the subset of patients with additional parametric imaging data (N=10) the planned analysis of parametric imaging parameters (see first secondary endpoint) is planned prior to completion of the study. This exploratory analysis of this secondary endpoint will not assess the primary endpoint and will not influence further trial conduct or further trial process.

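### Scan order is the only randomised factor, yet no stated analysis uses it: add a period term to the mixed models and a by-sequence sensitivity analysis (minor)

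*Protocol*

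**What the plan says.** The synopsis (Study Product / Intervention) states that "patients will be randomised to one of two tracer sequences". Section 6.2.1, under methods of minimising bias, defines group A as new tracer first and group B as standard tracer first, and adds: "A simple randomisation will be performed by the trial statistician using generation of a random number". It mentions neither blocking nor an allocation ratio. On patients who leave before the second scan, section 7.4.2 says "that patient will be replaced and recruitment will continue until 100 patients have been recruited", with no rule about balance between the sequences.

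Section 11.4.2 compares the tracers "using an absolute risk difference (new tracer minus old tracer) with a one-sided lower 95% confidence interval (CI) for paired proportions", over all pairs together. The tumour-to-background ratio (TBR) is analysed with a "linear mixed-effects regression model with tracer as fixed covariate and patient and region as nested random effects". The Poisson models for lesion counts likewise have tracer as their only fixed covariate. Section 11.4.1 refers to the randomised group when it defines the full analysis set. Those groups are scan orders, however, and no analysis in section 11.4 has a term for order, period or sequence.

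**The concern.** Randomising the order balances an order effect on average over repeated trials. In one trial it cancels exactly only if the two sequences are the same size or the analysis accounts for order. Simple randomisation does not force equal sizes, and the stated analyses do not use order. If the second scan were systematically more or less often positive than the first, part of that difference would be counted as a tracer difference. The decision rests on one confidence limit against −10 points, so a small displacement could matter when the result is close.

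An order effect is conceivable. The first scan is reported to the treating physician (section 3.7.2), and the second may follow up to two weeks later. The criterion against a change of prostate cancer treatment between scans (section 7.1) does not expressly cover diagnostic procedures.

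**Working it through.** **Inputs.** From the protocol: N = 100, margin −10 points, 80% positive on each tracer and 75% on both, hence 5% discordant in each direction (section 11.2). Assumed: 1:1 allocation, and an order effect π (second minus first scan, in positivity) of 2, 5 or 10 points, because the protocol gives none.

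**The plan's own figure.** Section 11.2 states: "With 100 patients we will have a power of 85% to detect non-inferiority". The Bonett–Price limit uses a = (n10 + 1)/(N + 2), b = (n01 + 1)/(N + 2), d = a − b, and lower limit d − z·√[(a + b − d²)/(N + 2)]. Exact enumeration with both discordant cells at 5% and z = 1.96 gives power 86.5%. The Monte Carlo standard error of 1000 repetitions is about 1.1 points, so 85% is reproduced. The one-sided 2.5% level of section 11.2 is used throughout.

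**Where order enters.** Let τ be the tracer effect (new minus old). The expected paired difference is τ − π in A and τ + π in B. Pooled over the realised trial:

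(nA(τ − π) + nB(τ + π))/N = τ + π(nB − nA)/N.

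**How unequal the sequences will be.** With nA distributed Binomial(100, 0.5):
- exactly 50:50 has probability 8.0%, so unequal 92.0%
- 55:45 or worse: 36.8%
- 60:40 or worse: 5.7%
- mean |nA − nB| = 8.0 patients

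**Size of the shift** (percentage points, either sign):

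| Assumed π | 55:45 | 60:40 | Mean over splits |
| --- | --- | --- | --- |
| 2 | 0.2 | 0.4 | 0.16 |
| 5 | 0.5 | 1.0 | 0.40 |
| 10 | 1.0 | 2.0 | 0.80 |

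For example, 5 × (60 − 40)/100 = 1.0.

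**Effect given the split.** The shift is applied to the exact enumeration. The wrong-claim column takes a true difference of −10 points with 5% and 15% discordant (assumed).

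| Shift | Power at no true difference | Wrong claim at −10 |
| --- | --- | --- |
| −1.0 | 78.9% | 1.6% |
| −0.5 | 82.9% | 2.1% |
| 0 | 86.5% | 2.7% |
| +0.5 | 89.6% | 3.5% |
| +1.0 | 92.1% | 4.4% |

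A simulation that keeps the sequences separate agrees on power: with π = 5 points and a 60:40 split, the pooled analysis has power 79.1% or 92.4%, depending on which sequence is larger. The equally weighted by-sequence analysis has 85.8% or 84.2%.

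**Effect over the randomisation.** Under simple randomisation each patient falls in A or B with probability one half. Suppose the order effect moves π/2 between the two discordant cells. At −10 points the cells are 5% − π/2 and 15% + π/2 in A, and 5% + π/2 and 15% − π/2 in B. Their average is 5% and 15% whatever π is. The pooled counts therefore have the same distribution as with no order effect, and the wrong-claim rate stays at 2.7%. The same argument leaves power at 86.5%.

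**Cost of using order.** With equal variances, the ratio of the by-sequence standard error to the pooled one is ½√(N/nA + N/nB): ½√(100/45 + 100/55) = 1.005, and ½√(100/40 + 100/60) = 1.021.

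**The case against.** The strongest reply is that nothing here damages the validity of the primary test. The sign of nB − nA is random, the estimate is unbiased over the randomisation, and the paired variance already contains the spread between sequences. The 3.5% and 4.4% arise only by conditioning on an unfavourable split, as can be done with any chance imbalance. This stands. A reader might infer that the plan inflates the false non-inferiority rate; the calculation does not support that.

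The design also limits any order effect. The scans are 2 to 14 days apart, a treatment change between them is ruled out (section 7.1), and separate readers handle each tracer, blinded to the clinical report (section 6.1.2). Reading order is randomised too (section 9.2.1). This stands as well. Five points is large beside a plan that expects only 5% discordance in each direction from all causes.

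A reader might further infer that simple randomisation is a mistake, or that replacing drop-outs worsens the balance. Neither is supported. Simple randomisation is the least predictable scheme, which suits an open-label single-centre trial, and blocks would trade some of that for balance. Section 7.4.2 does not say how a replacement is allocated.

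Finally, an analysis plan that is not shown could add a by-sequence sensitivity analysis, and nothing in the protocol rules one out. This stands only in part: section 11.4.2 writes out the covariates of the mixed models, and period is not among them.

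**Conclusion.** The point holds as a minor improvement. The protocol randomises scan order and then states no analysis that uses it. In the realised trial a fraction (nB − nA)/N of any order effect passes into the tracer difference: 0.2 to 1.0 points at 55:45 and 0.4 to 2.0 points at 60:40 for assumed effects of 2 to 10 points, against a 10-point margin. It could matter only for a borderline result together with a marked split and a real order effect, and the protocol gives no evidence of such an effect. Overall bias is nil and the overall error rate is not raised. The figures rest on 1:1 allocation, the assumed effect sizes, and the discordance stated with each calculation. They do not justify replacing the primary interval or the randomisation method.

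**What to change.** In section 11.4.2:

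- Add period (first or second scan) as a fixed effect to the Poisson lesion-count models and the linear TBR model.
- Prespecify a sensitivity analysis of the primary outcome: the equally weighted mean of the two sequence-specific paired differences, (dA + dB)/2, with standard error ½√(vA/nA + vB/nB), where v is the within-sequence variance of the paired differences. Use the same confidence level as the primary analysis, and state any small-sample adjustment within sequences.

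Keep the Bonett–Price interval as primary and keep simple randomisation. The change is a few lines of text and can be made after recruitment has started. Its statistical cost falls on the sensitivity analysis: a standard error about 0.5% larger at 55:45 and 2% larger at 60:40. In simulation without an order effect, power was 85.6% by sequence against 86.6% pooled. The primary analysis loses nothing.

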### Blinding procedures

Data collection will occur as follows:

1. Each individual patient will be assigned a unique patient identifier. Only the sponsor will have access to the “key”.

2. Imaging data will be coded and collected centrally by the sponsor. Coded and randomised data-sets will be provided to the readers at separate reading sessions. Data will be recorded separately on the CRF and the readers will not have access to each other’s results.

3. Once all data has been collected and the centralised reading is closed by the sponsor, the patient details will be unblinded to allow data analysis and clinical follow-up by the PI and his team of physician-investigators as named above.

4. The investigators will read each scan in a blinded fashion, and separately. The investigators will not have access to each other’s results.

### Other methods of minimising bias

Patients will be independently randomised before the first scan is performed.

Reading for each tracers is blinded as above.

## Unblinding Procedures (Code break)

Not applicable.

# STUDY POPULATION

This single centre study will take place in the setting of a university hospital for nuclear medicine (Inselspital, Bern). The initial scan is performed in accordance with clinical routine, and is reimbursed by the patient’s insurer. Adult males with biochemically confirmed recurrent prostate cancer will be recruited. Only adults capable of informed consent and able to schedule and attend two consecutive scans are eligible.

## Eligibility criteria

*Inclusion Criteria*

- Patients with known biochemical recurrence of a histologically confirmed prostate cancer post radical prostatectomy, defined as two consecutive PSA values > 0.2 ng/ml:
- Post prostatectomy: Patients > 18 y/o
- PSA measured within ± 4 weeks of the first PSMA-PET/CT
- Patients providing written informed consent
- No change in PC treatment in the period between the first and second scans

*Exclusion Criteria*

- Patients receiving ADT within 6 months prior to the PSMA-PET/CT
- Patients with contraindication to diuresis with 20mg Furosemide
- Patients with renal dialysis or relevant renal impairment (eGFR < 35 ml/min)
- Inability to provide written informed consent
- Inability to schedule and attend two consecutive PET examinations
- Patients undergoing active treatment for a second non-prostatic malignancy at the time of the first scan.
- Known sensitivity or allergy to PSMA-ligands or one of the components of the radiotracer solutions used.

## Recruitment and screening

Patients referred for clinically routine PSMA scanning for biochemically recurrent prostate cancer are screened for eligibility by an investigator. The recruitment procedure is outlined in detail in §9.3.

## Assignment to study groups

Randomisation and allocation sequence will be performed by the trial statistician who will hold the randomisation sequence, to which the investigators will not have access.

## Criteria for withdrawal / discontinuation of participants

Patients will be withdrawn immediately from the trial if informed consent is withdrawn. Patients who die in the follow up phase will be discontinued, but not withdrawn from the trial (since follow-up to composite standard is a secondary endpoint only). Patients who, during the study, undergo active treatment for a second non-prostate malignancy will be withdrawn from secondary endpoint analysis.

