## Secondary Outcomes

- Intra-individual comparison of the parametric imaging parameter K*_D_* (measure of tracer affinity) for the two radiotracers for n=10 patients.
- The number of pathological, benign and uncertain lesions for each tracer in five regions (prostate bed, pelvic lymph nodes, extra-pelvic lymph nodes, bone, or other organs) classified by six blinded readers (three for each tracer) using previously published interpretation guidelines (PSMA-Rads 1.0)
- Inter-reader reliability between the three readers for each tracer on the level of the region with respect to three categories (pathological, benign, uncertain).
- The region-based positive predictive value (PPV), i.e. the percentage of pathological lesions that are confirmed pathological at the 6 month follow-up (based on the subset of patients and lesions with follow-up data at 6 months).
- Tumour visibility will be compared by means of uptake values (SUV) as well as tumour to background contrast in a lesion based analysis. The tumour to background ratio (TBR) is defined as lesion SUV and SUV÷ SUV of reference background region, where the background uptake is defined by convention as the left gluteal musculature.
- Number and severity of adverse events per tracer (up to 48h follow-up, see below)

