## Safety Outcomes

We do not anticipate any adverse events. No known mechanism for anaphylaxis is known. However, in the unlikely case of an adverse event type (codified according to MedDRA) and severity of side effects will be recorded. Each patient receiving a scan will be evaluated for safety. The patient will be interviewed before and after the scan and spontaneous reports of adverse events reported to the investigator by patients and at the 48h follow up with the study nurse.

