### Response Criteria

Response to targeted treatment (surgery, radiotherapy) will be considered as confirmatory in the case of a fall in PSA, using previously published response criteria [22]. Where PET scan findings are recorded as positive, but the follow up refutes this, the scan will be recorded as false positive. Established RECIST (Vers 1.1) criteria will be used to interpret correlative imaging [23]. The details are as follows:

Follow up of clinical notes to 6 months will be performed for histopathological data, additional conventional imaging (CT, MRI and or bone scintigraphy), PSA change following focal salvage therapy (where no systemic therapy has been applied. Follow-up imaging will be performed by local read.

1. **Follow up histology**

Positive biopsy or histology will be taken to be confirmatory.

For negative biopsies: to rule out false negative imaging for image-guided biopsy will be reviewed. For lymph node biopsies, comparison of the PET/CT and follow-up (post intervention) imaging will be made to confirm that biopsy of the correct node occurred.

1. **Follow up imaging**

No established imaging criteria are available for a number of imaging modalities in recurrent prostate cancer. To enable comparison of these data with previous imaging trials, the imaging criteria as previously published by Fendler et al. will be used (§2.1.5.3 of Supplementary Materials 2: Trial Protocol [24])

1. **Follow up following local treatment**:

PSA change following radiation therapy will be according to previously published criteria, with a PSA response of > 50% taken to be confirmatory [25] (see figure 4).

[figure not shown]

**Fig.4.** Example interpretation criteria for patients undergoing biopsy or radiotherapy (with and without systemic hormone deprivation therapy) image from Emmett et al. [25]

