# SAFETY

## Drug studies

All adverse events (AEs) and all serious adverse events (SAEs) are collected, fully investigated and documented in source documents and case report forms (CRF) up until the follow up 48h post the second scan.

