### Datasets to be analysed, analysis populations

The full analysis set will include all randomised patients. They will be analysed according to the group they were randomised to regardless of the tracer actually used according to the intention-to-treat principle. We will also define a per-protocol analysis set that excludes major protocol violations.

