### Safety analysis

The number and severity of adverse events (up to 48h post exam) will be summarised by tracer using descriptive statistics. All serious adverse events will be listed.

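### Section 7.4 withdraws patients treated for a second malignancy from secondary endpoint analysis without limiting the endpoints: it conflicts with the safety and analysis-set rules and can remove false positives from the PPV

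*Protocol*

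**What the plan says.** The rule is one sentence in section 7.4: "Patients who, during the study, undergo active treatment for a second non-prostate malignancy will be withdrawn from secondary endpoint analysis". It comes straight after the rule for deaths in follow-up, which are discontinued but not withdrawn because composite follow-up is only a secondary endpoint.

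The secondary outcomes in section 5.2 are K_D, lesion counts by region, inter-reader reliability, region-based PPV, SUV and tumour-to-background ratio, and "Number and severity of adverse events per tracer (up to 48h follow-up, see below". The PPV is "the percentage of pathological lesions that are confirmed pathological at the 6 month follow-up".

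Other sections bear on the same patients:

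- Section 5.4: "Each patient receiving a scan will be evaluated for safety".
- Section 10.1: "All adverse events (AEs) and all serious adverse events (SAEs) are collected, fully investigated and documented in source documents", up to 48 hours after the second scan.
- Section 11.4.1: "The full analysis set will include all randomised patients". Section 11.4.3 gives the per-protocol set a secondary role.
- Section 11.4.6: adverse events are summarised by tracer, and "All serious adverse events will be listed".
- Section 6.1.4: "Where PET scan findings are recorded as positive, but the follow up refutes this, the scan will be recorded as false positive".
- Section 11.4.2: the PPV denominator is all lesions whose state is known.

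Section 7.1 excludes at entry only patients under active treatment for another malignancy at the first scan. A cancer found or treated later therefore falls under section 7.4.

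**The concern.** This is a post-randomisation exclusion triggered by an event that can come months after both scans. The study runs through follow-up, which is 6 months in sections 5.2, 6.1.2 and 6.1.4 and twelve months in section 6.1.3 and the synopsis. Treatment of another cancer in that period cannot invalidate images already read or a 48-hour safety contact already made.

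The rule also differs from its neighbours. A patient who withdraws consent keeps his data up to withdrawal (sections 7.4.2, 8.5 and 11.5). A consenting patient treated for a second cancer would, read literally, contribute less to the secondary endpoints than one who withdrew consent after both scans. No reason is given.

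The PPV is the more serious statistical matter. It asks whether findings rated pathological turn out to be prostate cancer. If a finding turns out to be a different cancer and that cancer is treated, the answer to the question is what removes the patient. Inclusion in the analysis then depends on the outcome being measured.

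**Working it through.** The plan states no figure on this point: no rate of second malignancy, no expected PPV and no number of lesions with follow-up. The check is therefore a comparison of sections, followed by an illustration on assumed inputs.

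**Step 1. Which endpoints the wording reaches, and when their data are complete**

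| Secondary endpoint (5.2) | Data source | Normally complete before a later second-cancer treatment? |
|---|---|---|
| K_D (n=10) | dynamic scans | yes |
| Lesion counts | blinded reads of the two scans | yes |
| Inter-reader reliability | same reads | yes |
| SUV and tumour-to-background ratio | same scans | yes |
| Adverse events | contact up to 48 h | yes |
| PPV | records during follow-up | no |

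Only one of the six endpoints depends on what happens during follow-up. The exception to the third column is treatment that starts in the 2 to 14 days between the scans. Section 7.1 requires no change in prostate cancer treatment in that interval but is silent on treatment of another cancer.

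**Step 2. Conflict under the literal reading**

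Section 7.4 takes these patients out of an analysis that includes adverse events. Sections 5.4, 10.1 and 11.4.6 evaluate, collect and report safety with no such exception. Section 11.4.1 puts all randomised patients in the full analysis set, whereas section 7.4 removes some of them from five scan-based or 48-hour endpoints. The sections cannot all be followed.

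**Step 3. What remains under the narrow reading (PPV only)**

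Take a focus rated pathological that follow-up shows to be another cancer. Its state is known, so it belongs in the denominator of section 11.4.2. Follow-up has refuted it, so section 6.1.4 makes it a false positive. Once that cancer is treated during the study, section 7.4 removes the patient. No other section puts the finding back.

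**Step 4. Illustration of the effect on PPV**

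Let TP and FP be the confirmed and refuted positive findings of known status, and k the false positives removed.

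- PPV with all patients kept = TP / (TP + FP)
- PPV under the rule = TP / (TP + FP − k)

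All inputs below are assumptions.

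| Findings (TP + FP) | PPV, all kept | k = 1 | k = 2 | k = 3 |
|---|---|---|---|---|
| 30 (24 + 6) | 80.0% | 24/29 = 82.8% | 24/28 = 85.7% | 24/27 = 88.9% |
| 50 (40 + 10) | 80.0% | 40/49 = 81.6% | 40/48 = 83.3% | 40/47 = 85.1% |
| 80 (64 + 16) | 80.0% | 64/79 = 81.0% | 64/78 = 82.1% | 64/77 = 83.1% |
| 30 (27 + 3) | 90.0% | 27/29 = 93.1% | 27/28 = 96.4% | 27/27 = 100% |
| 50 (45 + 5) | 90.0% | 45/49 = 91.8% | 45/48 = 93.8% | 45/47 = 95.7% |
| 80 (72 + 8) | 90.0% | 72/79 = 91.1% | 72/78 = 92.3% | 72/77 = 93.5% |

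The rise is between 1.0 and 10.0 percentage points.

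**Step 5. True positives leave with the patient**

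With 50 findings, PPV 80% and k = 3, suppose each removed patient also had one true positive. The PPV is then (40 − 3) / (50 − 6) = 37/44 = 84.1%, instead of 85.1%. If the second cancers were not PSMA-positive and three patients with one true positive each were removed, the PPV would be 37/47 = 78.7%, which is below 80%. The upward direction therefore depends on the second malignancy having been read as a pathological finding.

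**The case against.** Four counter-arguments deserve weight.

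**Adverse events.** A reader might infer that the rule deletes these patients' adverse events. The documents do not support that. Safety has its own sections, collection runs to 48 hours after the second scan, and serious events are listed without exception. What stands is an unresolved contradiction about who is in the safety analysis, not a certain loss of data.

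**Intended scope.** The preceding sentence in section 7.4 refers to composite follow-up as a secondary endpoint, so the authors may have meant only that endpoint, where treatment of another cancer can confound verification. This is plausible and would remove the conflict over counts, agreement and safety. It would not remove the PPV problem, because PPV is the follow-up endpoint.

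**Direction and tracer.** A reader might infer a general upward bias, larger for 18F-PSMA-1007, because section 3.4 reports more non-prostatic uptake with that tracer. That goes too far. Section 3.4 does not concern second malignancies. Benign non-specific uptake never triggers section 7.4, and removing a patient takes out both tracers' data. A difference between tracers would arise if a second cancer were rated pathological on one scan and not on the other; nothing in the protocol shows how often that happens.

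**Classification.** Section 6.1.4 also takes positive histology as confirmatory without saying of which cancer. Calling another malignancy a false positive is the sensible reading of a prostate cancer PPV, but it is not spelled out. This is a further reason to state it.

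The verification is also exploratory (section 9.2.2) and limited to patients with clinically driven follow-up. That bears on severity, not on whether the sentence needs correction.

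**Conclusion.** The point holds as a defect of scope and of outcome-dependent exclusion. On the literal reading, section 7.4 discards usable scan-based and 48-hour data and contradicts sections 5.4, 11.4.1 and 11.4.6. On the narrow reading, it can still remove refuted findings from the PPV.

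The upward bias requires that the second malignancy was PSMA-positive, was read as pathological, was shown by follow-up not to be prostate cancer, and was treated during the study. Its size cannot be derived from the documents; the rise of 1 to 10 points rests on assumed numbers and on only false positives being lost. The same patients' true positives are lost too, and a tracer difference is possible but not shown.

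The primary endpoint is outside the rule and is unaffected. Severity is moderate.

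**What to change.** Replace the sentence in section 7.4 with a rule to this effect:

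- Patients treated for a second non-prostate malignancy during the study stay in all endpoints measured on the scans or within 48 hours of them. The safety analysis includes every scanned patient.
- In the PPV, a PSMA-positive finding rated pathological and shown to be a non-prostate malignancy counts as not confirmed (false positive).
- A lesion is not evaluable only if its sole verification is PSA change or imaging obtained after treatment of the other cancer began.
- If that treatment starts between the two scans, the patient is handled through the per-protocol set or a sensitivity analysis.

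The cost is one amended sentence and the matching analysis rule, with minor additional analysis work. No new data, patients or procedures are needed. The reported PPV may be slightly lower than under the present rule.
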